**Methods:**

The clinical study (DRKS00026624) includes two randomized controlled intervention trials with parallel groups, for patients with elective cardiac catheterization and practitioners at the catheterization lab, in two clinic sites of the Ernst-von-Bergmann clinic network in Brandenburg, Germany. Both groups received different interventions for stress management. The intervention for patients comprises a psychoeducational video with different stress management technics and additional a standardized medical information about the cardiac catheterization examination. The control condition includes the in hospitals practiced medical patient education before the examination (usual care). Primary and secondary outcomes are measured by physiological parameters and validated questionnaires, the day before (M1) and after (M2) the cardiac catheterization and at a postal follow-up 6 months later (M3). It is expected that people with standardized information and psychoeducation show reduced complications during cardiac catheterization procedures, better pre- and post-operative wellbeing, regeneration, mood and lower stress levels over time. The intervention for practitioners includes a Mindfulness-based stress reduction program (MBSR) over 8 weeks supervised by an experienced MBSR practitioner directly at the clinic site and an operative guideline. It is expected that practitioners with intervention show improved perceived and chronic stress, occupational health, physical and mental function, higher effort-reward balance, regeneration and quality of life. Primary and secondary outcomes are measured by physiological parameters (heart rate variability, saliva cortisol) and validated questionnaires and will be assessed before (M1) and after (M2) the MBSR intervention and at a postal follow-up 6 months later (M3). Physiological biomarkers in practitioners will be assessed before (M1) and after intervention (M2) on two work days and a two days off. Intervention effects in both groups (practitioners and patients) will be evaluated separately using multivariate variance analysis.

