Although there is still only limited research on stress-reducing interventions in catheterization labs, a few studies on psychological preparation and video-based psycho-educative interventions in patients have shown beneficial results concerning pre- and perioperative distress, anxiety and coping as well as postoperative recovery and wellbeing (34–37). Less stressed and anxious patients may lead to less complications and reduced durations of cardiac catheterizations that could be beneficial for both patients and practitioners. A lower risk of complications and well-prepared patients may reduce the distress and pressure on the staff at the catheterization lab that in turn could be beneficial for patient safety and therapeutic outcome. To the best of our knowledge, there is no study protocol or study on stress-management in clinical settings that address both group—practitioners and patients—simultaneous. We expect a positive, bidirectional influence from both interventions to both intervention groups.

The objective of the study is to develop and implement an intervention for both practitioners and patients that aims to reduce the physical and psychological strain of a cardiac catheterization. This study tries to answer the following research questions:

Whether and to what extent are cardiac catheterization interventions physically and psychological stressful for both patients and practitioners?Whether and to what extent does a standardized video-based patient education lead to less stress, anxiety, surgical complications, postoperative hospitalization, as well as better recovery, compliance and well-being?Whether and to what extent can practitioners benefit from operational guidelines at the catheterization lab and a stress management intervention in terms of reduced stress during work at the catheterization lab and a faster recovery after a workday?

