## Methods and Analysis

### Study Design

The multicenter study “Heartbeat” implement a randomized and controlled pre-post-study design involving two intervention trials with parallel groups, for patients with elective cardiac catheterization and practitioners at the catheterization lab, respectively (Figure 1, DRKS No: 00026624^1^). The patient study with a 1:1 randomization by person and a standard treatment control group involves three measurement points: the day before (M1 = admission day) and the day after the video-based stress management intervention and cardiac catheterization examination (M2 = CC examination day), and 6 months after baseline (M3). The MBSR intervention trail for the practitioners at the CC lab involves a 1:1 randomization by group and a no-treatment control group with three measurement points: before (M1) and after the 8-week (M3) intervention with a mindfulness-based stress reduction program, as well as 6 months after baseline (M3). The study takes place at the two clinic sites of the Ernst-von Bergmann community clinic, in Potsdam (patients and practitioners) and Bad Belzig (only patients). The time of data collection is estimated with ~1 h for all questionnaires and 2 days for the physiological measurements (practitioners). The data collection period is planned from 01/2021 to 12/2022.

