*The intervention for practitioners* includes an 8-week Mindfulness-based stress reduction (MBSR) program based on the Jon Kabat-Zinn method (39, 40), which take place weekly for 1.5 h. For the first 6 weeks, the intervention is supervised by an experienced MBSR practitioner directly at the clinic site. The following 2 weeks, it takes place at home guided by an audio guide and an exercise book. The MBSR program includes body scan, sitting meditation and Hatha-yoga exercises, as well as breathing exercises throughout all three types of meditation. During the body scan every part of the body is systematically and conscious sensed in a lying position to enhance mindfulness. Key component of the sitting meditation is the upright position and conscious focus on breathing and staying in a mindful state. The different yoga poses (asanas) comprise balance and stretching elements for lying and upright positions. The exercise within MBSR differs from week to week with regard to the yoga elements, but every single routine starts with body scan and sitting meditation.

Additionally, an operative guideline for interaction with colleagues, conduct during and after complications and traumatic events during a cardiac catheterization examination was developed on basis qualitative interviews with staff members of the catheterization lab prior to the study. These guidelines for mindful and self-aware behaviors are printed and hang out as a poster at the catheterization lab.

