## Discussion

The randomized control intervention study presented in this protocol will test the effectiveness of stress management interventions for both patients who undergo elective cardiac catheterization and practitioners who work in the catheterization lab. The intervention for patients comprises a video-based standardized information about the cardiac catheterization examination and a patient psychoeducation with stress management techniques like relaxation, meditation and guided imagery as well as cognitive distraction and reframing. The intervention video is presented at the admission day before the cardiac catheterization. The intervention for practitioners includes an 8 weeks Mindfulness-based stress reduction (MBSR) program with body scan, sitting meditation, Hatha-yoga and breathing exercises for 90 min per week at the clinic site and at home. Additionally, operative guidelines for mindful and self-aware behaviors during the catheterization procedure and in case of complications and adverse events are evolved and presented at the lab. Generally accepted and validated instruments and questionnaires are implemented to measure the effect of the intervention.

Although cardiac catheterizations are one of the most frequently used standard diagnostic procedures in invasive cardiology, there are only a few studies that analyse stress management interventions for practitioners at catheterization labs and only a few methodological reliable and up-to-date intervention studies that analyse video-based psychoeducative interventions (9). Given that burnout is reported by 50% of cardiologists and that this trend is driven by systemic demands and inefficiencies of the healthcare system (61), practitioners at catheterization labs seem to be a risk group of chronic stress and all health consequences that come along with it like sleep disorders, depression, cardiovascular diseases, obesity, Type-2 diabetes (62).

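### As described, practitioner controls are exposed to the guideline poster, so the randomised contrast is MBSR added to the guideline, not the package against no treatment

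*Protocol article*

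**What the plan says.** The Abstract (Methods) lists two components of the practitioner intervention, an 8-week course "supervised by an experienced MBSR practitioner directly at the clinic site and an operative guideline". The third research question in the Introduction covers both: it asks to what extent "can practitioners benefit from operational guidelines at the catheterization lab and a stress management intervention in terms of reduced stress".

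For the comparator, Study Design says that the practitioner trial "involves a 1:1 randomization by group and a no-treatment control group with three measurement points". The same section gives the locations: the study runs "in Potsdam (patients and practitioners) and Bad Belzig (only patients"). Participants and Sample Size Determination confirm that the practitioner sample is the eligible staff of that one laboratory.

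On delivery, Experimental Procedure/Intervention describes the guideline under the practitioner intervention, as covering dealings with colleagues and conduct around complications and traumatic events. It then states: "These guidelines for mindful and self-aware behaviors are printed and hang out as a poster at the catheterization lab". The Discussion repeats that the guidelines for conduct "in case of complications and adverse events are evolved and presented at the lab".

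On conclusions, the discussion part of the Abstract says that the stress management guidelines should move into clinical routine. The close of the Discussion says the same and calls the guidelines evaluated.

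**The concern.** Three statements do not fit together: the guideline is part of the tested intervention, it hangs where both arms work, and the control group has no treatment. If controls work beside a component of the intervention, the label on the comparator is wrong, and so is the reading of any difference between the arms.

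What is at stake is what the trial may conclude. A reader who takes the design at its word will read the arm difference as the effect of the whole programme against nothing. That reader will also accept the guideline as having been tested in a randomised comparison before it is recommended for routine use. The design as described supports neither reading.

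**Working it through.** The practitioner trial has no stated sample size or power, so there is no figure to reproduce. The check sets the statements side by side and then works out what the arm contrast estimates.

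**Step 1: who is exposed to what.**

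| Element | Intervention arm | Control arm | Source |
|---|---|---|---|
| MBSR course | yes | no | Abstract; Experimental Procedure/Intervention |
| Guideline poster | in the shared laboratory | in the same laboratory | Experimental Procedure/Intervention; Discussion |
| Workplace | Potsdam laboratory | Potsdam laboratory | Study Design; Participants; Sample Size Determination |
| Stated label | MBSR and guideline | no treatment | Abstract; Study Design |

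No section limits the poster to one arm, room or shift. Randomising by group does not separate the arms either, because every group is formed from the same staff.

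**Step 2: what the contrast estimates.** Write Y(m, g) for the mean outcome with MBSR (m = 1) or without (m = 0), and with the guideline (g = 1) or without (g = 0).

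- Package against nothing, as labelled: Y(1,1) − Y(0,0).
- Contrast with controls fully exposed: Y(1,1) − Y(0,1), the effect of MBSR where the guideline is present.
- Difference between the two: Y(0,1) − Y(0,0) = G, the effect of the guideline in staff without MBSR.

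If a share e of G reaches controls, the arm contrast falls short of the package effect by e × G. If the effects also add, with M for MBSR, the contrast is M + G − e × G.

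**Step 3: illustration.** The documents give no value for M, G or e. The values below are assumptions, with M + G fixed at 0.5 SD.

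| M | G | e = 0 | e = 0.5 | e = 1 |
|---|---|---|---|---|
| 0.5 | 0 | 0.5 | 0.5 | 0.5 |
| 0.3 | 0.2 | 0.5 | 0.4 | 0.3 |
| 0 | 0.5 | 0.5 | 0.25 | 0 |

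For example, M = 0.3, G = 0.2 and e = 0.5 give 0.3 + 0.2 − 0.5 × 0.2 = 0.4. The first row shows no loss when the poster does nothing. The last shows the contrast vanishing when the poster does everything and reaches all controls. The table shows the mechanism and is not an estimate for this trial.

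**Step 4: whether another planned analysis fills the gap.** Statistical Analysis plans a within-person comparison before and after the intervention, for the physiological data. In controls, such a change mixes the guideline with time. In the intervention arm it adds MBSR to that mixture. If the poster was already up at M1, M1 is not a pre-guideline value, and the change misses the introduction of the poster. The planned comparison with German population norms describes the level of stress, not the effect of a guideline. Neither analysis gives randomised evidence on the guideline.

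**The case against.** The strongest counter-argument is that the randomised element is already presented mainly as MBSR. Study Design names the practitioner trial after MBSR, the Abstract times measurements by the MBSR course, and the guideline is introduced as an addition. Practitioner data are to be analysed mainly descriptively, and no separate test of the guideline is stated. This lowers the weight of the point but does not remove it. Inferential statistics on group differences are still planned, the third research question names the guideline, and the transfer statements include it.

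It can also be said that staff may ignore a poster, and that the article does not say when it was hung. That stands: the text supports exposure as described, not proven uptake.

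Three stronger readings are tempting, and the documents do not support them.

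- A reader might infer that the poster is the reason why the guideline's own effect cannot be estimated. In a two-arm trial of a package against nothing, that separate effect would not be estimable even with perfect separation of the arms. What shared exposure costs is the package contrast and a correct control label.
- A reader might put a percentage on the understatement. Any such figure only restates an assumed share of the effect due to the guideline, and the documents give no such share.
- A reader might conclude that the poster should be withheld from controls. The guideline concerns conduct between colleagues, so giving it to half of one team would not keep it from the other half. Study Status also reports that the first practitioners have been recruited and assessed.

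**Conclusion.** The point holds as a mislabelled comparator and an over-wide conclusion. On the article's own description, the randomised practitioner contrast estimates MBSR added to the guideline. It does not estimate the combined package against no treatment and provides no randomised evidence on the guideline.

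The effect of MBSR in the presence of the guideline remains estimable, so the practitioner comparison is not lost. The shortfall against the package effect is e × G. It is zero if the poster has no effect, grows with a beneficial effect and with uptake by controls, and cannot be quantified from the documents.

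The conclusion rests on two readings of the text: that the poster hangs in the laboratory where both arms work during the measured period, and that no unstated arrangement keeps controls from it. It should be corrected, but for a small and mainly descriptive trial the correction is one of wording.

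**What to change.** - In Study Design, describe the practitioner control as guideline-exposed (guideline only) in place of no treatment.
- Limit the third research question and all randomised conclusions for practitioners to the effect of MBSR added to the guideline.
- State when the poster was hung relative to M1.
- Report anything on the guideline as descriptive before/after findings only. If the poster was up before M1, say that M1 is not a pre-guideline measurement.
- In the discussion part of the Abstract and at the close of the Discussion, drop or qualify the statements that the guidelines have been evaluated and should be transferred into routine.

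The cost is a few sentences and one date, with no change to procedures, so it remains feasible with recruitment under way. The downside is that the claim of effectiveness for the guideline is given up.

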### Strategies to Improve Adherence to Interventions

As the intervention video takes only 10 min to watch, adherences strategies for the patients focusses on improved questionnaire return and complete data. To ensure that all questionnaires are completed and returned, a close relationship and support between participant and study staff are stablished. After recruitment, study education and informed consent, participants are asked to fill in the questionnaire for baseline and return it to the staff member. For after-intervention questionnaire (M2) this routine is assured by the nurses at the catheterization ward. To secure the follow-up measurement (M3, 6 months after baseline), a study member contacts the participants via telephone call and sends the questionnaire by post with a prepaid envelope for the return. For the practitioners the adherence strategy focusses on a low-threshold and time-saving training intervention directly at clinic side. Furthermore, adherence problems and barriers are assessed in all follow-up questionnaire. The measurement of HRV on two lab and two leisure days (before and after intervention) is realized by self-applied chest strap heart monitor, a smartphone and an app for the HRV measurement, all provided by the study staff.

### Outcomes

The primary outcomes for patients are reduced complications and less sedative medication during CC (documented by nurses at the CC lab), and less tension/strain (physiological parameters like pulse, blood pressure, heart frequency), perceived stress (PSS) and better mood (POMS) measured by established and validated self-report questionnaires. Further secondary outcomes for patients are better pre- and post-operative wellbeing, chronic stress (TICS), depression and anxiety (HADS), panic disorder, psychosocial functioning (PHQ-9), life events (ILE), general health (SF-12), satisfaction with health and sleep (41). Additionally, patients are asked about their life style, socioeconomic status and satisfaction about the intervention. At the CC lab, nurses document the behavior of the patients during the cardiac catheterization (agitation, duration of hospital stay, tranquilizer/sedativa use, and level of information) and the number of complications occurred during the procedure. The primary outcomes for practitioners—perceived (PSS) and chronic stress (TICS)—are measured by established and validated self-report questionnaires. Additionally, stress load and recovery are assessed by physiological measurements: circadian profile of HRV (42–44), saliva cortisol (45), alpha-amylase (46) and lysozyme on two working/lab days and two days off as well as the following night, prior to and after the intervention, respectively. The HRV measurements base on beat-to-beat R-R intervals and comprises outcomes for the total activity of the autonomic nervous system [standard deviation of RR intervals (SDNN)], parasympathetic function [root mean sum of squared distance (RMSSD)] and stress load and recovery (number and percentage of R-R intervals lower or >50 msec). Saliva samples are taken on nine defined time points during the day (immediately after awakening, 30, 45, 90, 150 min after awakening, before lunch, 4 p.m., before dinner and going to bed) on a working/lab day and day off. Weight and mood (POMS) are assessed simultaneously as control variables. The practitioners are further asked about vital exhaustion (VE), anxiety and depression (HADS), tension, effort-reward imbalances (ERI), social support (BSSS), satisfaction with health and sleep (41) as well as life style, socioeconomic status, expectations and adherence (barriers) to the intervention program.

Details on outcomes, questionnaires and measurement points are provided in Table 1 for participants and Table 2 for practitioners.

**Table 1 T1:** Outcome measurements for patients with elective cardiac catheterization.

**Outcome**	**Measurement**	**Assessment**		
		**M1** **(day before CC)**	**M2** **(day after CC)**	**M3** **(6 months after M1)**
Chronic stress	Trier inventory for chronic stress (TICS) (47)	X		X
Perceived stress	Perceived stress scale-−10 items (PSS-10) (48, 49)	X		X
Life events	Inventory of stressful life-events (ILE) (50)		X	
Depression	Patient health questionnaire-−9 items (PHQ-9) (51)	X		X
Anxiety and depression	Hospital anxiety and depression scale (HADS) (52, 53)	X	X	
Health-related quality of life	Short form health-−12 items (SF-12) (54)	X		X
Pain	Visual analog scale (VAS)	X	X	X
Mood	Profile of mood state (POMS) (55, 56)	X	X	
Satisfaction with health and sleep	Visual analog scale (VAS)	X	X	X
Life style factors	Physical activity, smoking, alcohol consumption, medication, critical life events	X		X
Sociodemographic characteristics	Sex, Age, education, marital status, job position, income	X		
Satisfaction with intervention			X	
Behavior while CC*				
Physiological parameter while CC*	Pulse, blood pressure, heart frequency	X	X	

**(additional) measurement during CC*.

**Table 2 T2:** Outcome measurements for practitioners at the catheterization lab.

**Outcome**	**Measurement**	**Assessment**		
		**M1** **(before intervention)**	**M2** **(after intervention)**	**M3** **(6 months after M1)**
Chronic stress	Trier inventory for chronic stress (TICS) (47)	X		X
Perceived stress	Perceived stress scale-−10 items (PSS-10) (48, 49)	X		X
Effort-reward imbalances	Effort-reward imbalances questionnaire (ERI) (57)	X		X
Anxiety and depression	Hospital anxiety and depression scale (HADS) (52, 53)	X	X	
Vital exhaustion	Maastricht vital exhaustion questionnaire (VE) (58)	X	X	
Tension	Visual analog scale (VAS)	X	X	X
Mood	Profile of mood state (POMS) (55, 56)	X	X	
Satisfaction with health and sleep	Visual analog scale (41)	X	X	X
Life style factors	Physical activity, smoking, alcohol consumption, medication, critical life events	X		X
Social support	Berlin social support scale (BSSS) (59)		X	
Sociodemographic characteristics	Sex, age, education, marital status, job position, income	X		
Expectation of/satisfaction with intervention		X	X	
Heart rate variability	Activity of the autonomic nervous system (SDNN), parasympathetic function (RMSSD)	X	X	
Stress profile	Cortisol, alpha-amylase (saliva samples) on nine defined time points during the day (two lab days and two days off)	X	X	
Weight	Scale	X	X	

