### Sample Size Determination

We calculated the sample size for two patient groups for two measurement points based on a pilot study. The sample was powered to assume a medium effect size (*d* = 0.25) and a minimum detectable clinical difference of 0.5 standard deviation on the (z-standardized) main criterion: perceived stress. For the main criterion, the power for significant group differences is 1-β = 0.93 with a case number of *N* = 60 people per group (38). As the sample for the practitioners was limited to all members of the catheterization lab of the clinic who fulfill the inclusion criteria, a sample size determination was not required.

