
*The intervention for patients* focusses on a video-based standardized patient information about the cardiac catheterization examination and further involves a short patient education with different stress management technics. The video-based standardized patient information gives information about the aim and general process of the CC, like location and aftercare of the puncture, position of the participants during the examination how the procedure is monitored. Further information comprises potential but rare complications and side effects like additional interventions, circulatory disruptions, cardiac arrhythmia, bleedings and (temporary) pain. The second part of the video broaches the issue of stress management technics to handle anxiety, tension and malaise. It provides brief instructions for relaxation, meditation and guided imagery techniques as well as cognitive distraction tasks, and cognitive reframing. All cognitive techniques are easy to apply after one presentation and involve methods to stop negative thoughts, distract from unhelpful thought patterns, to guide attention and positive expectations, to lower tension and support relaxation. For example, the patient should recite the alphabet and imagine a positive thing or event for every letter that he/her would be able to do after the CC. The patient should guide his/her attention to their most pleasant vacation and reactivate the feelings and thoughts present at that time. If a patient feels discomfort or pain, he/she should guide his attention to his/her big toe or left hand for cognitive distraction. The video encourages the patient to speak to the doctors and nurses about complaints and needed assistance. The video is shown to the patients the day before the CC via a tablet bedside in the clinic and is complementary to the non-standardized patient education by the medical doctor that is clinical routine for both intervention and control group.

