### Statistical Analysis

All statistical analyses will be performed using SPSS. The data of the practitioners will be mainly analyzed descriptively due to the small sample size. Interferential statistics will be used to identify group differences. A comparison with norms of the German general population will be performed to assess the stress of the practitioners in the cardiac catheter laboratory. Baseline and post-interventional physiological data like circadian profile slopes of HRV and derived indicators (SDNN, RMSSD, number and percentage of R-R intervals lower or >50 msec) as well as saliva cortisol, alpha-amylase and lysozyme measurements will be compared on an intraindividual level. The data of the patients will be analyzed according to a multivariate variance analysis (between-subject factor: intervention group vs. control group). Sociodemographic data, sedative medication, adherence to the intervention will be implemented as control variables or stratification variables for subgroup analysis. Statistical significance is set at *p* < 0.05 (two-sided) and effect sizes will be reported.

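### The patient trial declares five co-equal primary outcomes but is sized for perceived stress alone, and the planned multivariate analysis cannot plausibly join the five into one test.

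*Protocol article*

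**What the plan says.** **Outcomes.** The list opens with "The primary outcomes for patients are reduced complications and less sedative medication during CC" and continues with "less tension/strain (physiological parameters like pulse, blood pressure, heart frequency), perceived stress (PSS) and better mood (POMS"). All five stand on the same footing: complications, sedative medication, tension/strain, PSS and POMS. Tension/strain is not one defined variable; the word *like* introduces examples.

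**Sample Size Determination.** The calculation concerns one "z-standardized) main criterion: perceived stress". It gives 60 patients per group and a power of 0.93. No other primary outcome enters it.

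**Statistical Analysis.** Patient data go into a multivariate variance analysis with group as the between-subject factor. Its dependent variables are not named. Sedative medication appears here as a control or stratification variable. One level applies throughout: "Statistical significance is set at *p* < 0.05 (two-sided").

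**Table 1.** PSS is scheduled at M1 and M3, POMS at M1 and M2, and the physiological parameters at M1 and M2 with additional readings during the procedure.

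**Complications.** No expected rate is given. The description of the patient video says "Further information comprises potential but rare complications and side effects", and the Introduction treats catheterization as a low-risk routine procedure.

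**The concern.** The Outcomes and Sample Size sections give different answers to the question of which comparison decides the patient trial. With five co-equal primaries and one flat level, a favourable result on any of them could be reported as a positive primary result, while only perceived stress was considered in the sizing.

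Complications raise a separate problem. They come first among the primaries, and the abstract expects them to fall. If they are as uncommon as the article suggests, 60 patients per group will yield few events. A non-significant comparison would then look like a failed primary although it had little prospect of succeeding.

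**Working it through.** **1. The plan's own figure.** Inputs from Sample Size Determination: 60 per group, a difference of 0.5 SD (SD = 1), and an effect size also given as *d* = 0.25. Two-sided 0.05 comes from Statistical Analysis.

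- 0.5 SD: 0.5 / √(2/60) = 2.739; power = Φ(2.739 − 1.960) = 0.78.
- *d* = 0.25: 0.25 / √(2/60) = 1.369; power = Φ(1.369 − 1.960) = 0.28.

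Neither gives 0.93. A value near 0.93 appears if 0.25 is read as Cohen's *f* (equal to 0.5 SD) and an unstated correlation between the two measurements is added, for example 0.2 to 0.3 for the between-group effect over two time points (power 0.94 to 0.92). On any of these readings the figure concerns perceived stress only.

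**2. Can one multivariate test link the five?** Setting the sections side by side:

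- Sedative medication is a primary outcome in one section and a control variable in the other. It cannot be both in the same model.
- Complications are rare events, which suit a multivariate variance analysis poorly.
- After the intervention, PSS is measured only at M3 and POMS only at M2. They share no post-intervention time point.
- A significant joint test would not show which primary had succeeded.

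**3. Error if the outcomes are tested separately at 0.05.** For *k* independent outcomes the chance of at least one false positive is 1 − 0.95^k. The correlated values come from simulating normal test statistics with a common correlation, which is assumed.

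| Count | Independent | Corr. 0.3 | Corr. 0.5 | Corr. 0.7 | Bound, any dependence |
|---|---|---|---|---|---|
| 5 (outcomes as named) | 1 − 0.95^5 = 22.6% | 20.8% | 18.4% | 14.8% | 5 × 0.05 = 25% |
| 7 (three physiological examples counted apart) | 1 − 0.95^7 = 30.2% | 27.1% | 22.9% | 17.8% | 7 × 0.05 = 35% |

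**4. Complications at 60 per group.** Control rates and the halving are assumptions, because the article gives neither. The outcome is taken as yes/no per patient.

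| Control vs intervention | Expected control events | Power, Fisher | Power, normal approx. | n per group for 80% (normal approx.) |
|---|---|---|---|---|
| 2% vs 1% | 1.2 | 0.1% | 6.5% | 2319 |
| 5% vs 2.5% | 3 | 2% | 11% | 906 |
| 10% vs 5% | 6 | 9% | 18% | 435 |
| 20% vs 10% | 12 | 25% | 33% | 199 |

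Fisher's test needs at least 6 events against 0 for p < 0.05: 6 vs 0 gives p = 0.027, and 5 vs 0 gives p = 0.057.

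**5. Keeping all five as primaries instead.** Bonferroni over five means 0.05 / 5 = 0.01 each. In the simple two-group comparison, power for 0.5 SD at 60 per group falls from 0.78 to Φ(2.739 − 2.576) = 0.56. About 94 per group would be needed for 80%.

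**The case against.** A multivariate variance analysis is a joint test. If all primaries entered one model, the global error would stay at 5%. Rules for follow-up tests are usually left to an analysis plan, which is not shown, so the lack of an adjustment rule in the article is not itself a fault. Both statements are fair. They do not remove the conflict over which outcome is decisive, and the text makes a joint model of all five implausible.

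Several stronger readings are tempting but not supported:

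- *Seven or more primaries.* A reader might split tension/strain into its bracketed measures. The article names five outcomes; the measures are examples, and pulse and heart frequency are nearly the same quantity.
- *Each primary tested at 0.05.* This is an inference from the single stated level. The article does not say it.
- *A ceiling of 30% on the error.* That is the value for seven independent tests. The bound for seven is 35%, and positive correlation lowers the figure.
- *Complications cannot be tested.* The article gives no rate. Its word *rare* describes the content of the video, and the low-risk remark is general background. Outcomes records the number of complications, and a count analysis could differ from Fisher's test, which is conservative. Very low power is supportable; impossibility is not.
- *The same fault in the practitioner trial.* PSS and chronic stress (TICS) are both primary there, but those data are to be analysed mainly descriptively because the sample is small. The point is minor.

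It can also be objected that reduced complications are a hypothesised benefit, so demoting them to a safety listing would change the study question. That stands, and it is why they should remain a secondary efficacy estimate.

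**Conclusion.** The concern holds in this form: five declared patient primaries, one sized criterion, one flat level, and a multivariate analysis whose variables are unnamed and which cannot plausibly join the five. The inflation depends on separate testing at 0.05: about 23% if the five are independent, about 15% to 21% at assumed correlations of 0.7 to 0.3, and 30% only if the three physiological examples are counted apart and all seven tests are independent. Even the lowest of these is roughly three times the nominal 5%.

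For complications the conclusion is low information: Fisher power of 9% or less for a halving at assumed control rates up to 10%.

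The mismatch between the sections rests on the text and needs no assumption. The sizes rest on the assumptions stated. An analysis plan could supply a multiplicity rule, but it would not settle which outcome is primary or add power for rare events. The point should be settled before outcome data are analysed.

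**What to change.** - Make perceived stress, the criterion used for sizing, the single patient primary at a stated time point. As Table 1 stands, that is M3. Either state M3, or reconcile Table 1 with the sizing and with the Discussion's aim of lowering perceived stress during the procedure.
- Move sedative medication, physiology and POMS to secondary outcomes with Holm adjustment. Replace the open physiological list with a named measure and time, so that the family is closed. With three tests the Holm steps are 0.05/3 = 0.0167, 0.05/2 = 0.025 and 0.05.
- Do not use sedative medication as a control variable when it is an outcome. It arises after randomization and may be changed by the video, so adjusting for it could distort the group effect.
- Report complications as a secondary estimate of the group difference with an exact 95% confidence interval and no claim of a powered test.
- Name the dependent variables of the multivariate analysis.

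The cost is revised outcome wording and a registry update, and fewer outcomes can be called primary. Keeping PSS at M3 needs no extra patients or measurements; adding an M2 assessment would mean one more short questionnaire for patients not yet past that point.
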